## Abstract

**Background:**

Chronic hand eczema (CHE) is a prevalent inflammatory skin disease in clinical practice. Guidelines recommend the use of topical medications, including corticosteroids and calcineurin inhibitors; however, prolonged use of these drugs may result in adverse effects, such as skin atrophy, drug tolerance, and rebound phenomena. Moreover, these medications exhibit limited efficacy in managing chronic hypertrophic hand eczema. Traditional Chinese medicine (TCM) has a long history of treating patients. The Runzaozhiyang lotion (RZZYL) is often used in the Department of Dermatology of Guang'anmen Hospital, China Academy of Chinese Medical Sciences, for these patients, with marked efficacy on symptoms, keratinization, hypertrophy, and pruritus improvements. Nonetheless, there is still no high-quality evidence from evidence-based medicine to prove the effectiveness and safety of CHE treatment.

**Objective:**

This study aimed to examine the efficacy and safety of a classic Chinese herbal prescription, RZZYL, for CHE and to provide a different treatment option for patients with hand eczema who are resistant to conventional Western pharmaceutical treatments.

**Methods:**

This study is a clinical trial characterized as randomized, double-blind, double-dummy, and positive drug-controlled. A total of 122 patients diagnosed with CHE have been randomized and allocated in a 1:1 ratio into 2 distinct groups, with one receiving the intervention and the other serving as the control. Participants in the intervention group will receive RZZYL granules along with a placebo cream of mometasone furoate, whereas the control group will get mometasone furoate cream in combination with a placebo for RZZYL granule. Both groups will be treated with either the active drug or a placebo for 4 weeks. The primary outcome metrics are the Hand Eczema Severity Index (HECSI) and the Numerical Rating Scales (NRS). Secondary outcome metrics consist of the target lesion area score, the Patient-Oriented Eczema Measure (POEM), the Dermatology Life Quality Index (DLQI), and the Investigator Global Assessment (IGA). The outcomes will be assessed at the start of the study and again at 2 and 4 weeks after the treatment period.

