### Outcome Measures

Figure 2 shows the study timeline. As detailed below, all outcome measurements, along with drug administration and collection, will be documented from baseline to the conclusion of treatment.

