#### The Numerical Rating Scale

The numerical rating scale (NRS) is a horizontal line segment akin to the Visual Analog Scale, generally anchored at one end as “no itching” and at the other as “extremely itchy” or “the worst itching ever experienced,” with the end points marked as “0” and “10,” respectively. A score of 0 indicates the absence of itching while a score of 10 signifies the highest level of itching possible. A higher score indicates increased severity of itching. Patients report a numerical value reflecting the average intensity of itching experienced over the preceding 24 hours or the past week. Itching severity is categorized as no itching (score 0), mild itching (0<score <4), moderate itching (4≤ score <7), severe itching (7≤ score <9), and very severe itching (score ≥9).

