### Data Analyses

The results of this trial will be analyzed from three perspectives:

Full Analysis Set (Intention-to-Treat Analysis): This set includes all randomized participants, with data analyzed according to the principle of “randomization equals analysis.” Missing data will be addressed using multiple imputation methods. Predictive mean matching will be used for continuous variables while logistic regression imputation will be used for categorical variables.Per Protocol Set: This set comprises participants who meet specific criteria; that is, they must have completed at least 80% of the treatment regimen (ie, a minimum of 22 days of medication within 4 weeks), have not used prohibited study drugs, and possess complete data for the primary end point (HECSI score).Safety Set: This set includes all participants who received at least 1 dose of the study medication.

The variable processing and statistical methods for this trial are outlined as follows: (1) continuous variable data that adhere to a normal distribution will be presented as mean (SD). Independent sample *t* tests (2-tailed approach) will facilitate between-group comparisons while repeated measures ANOVA will be applied for comparisons across multiple time points (eg, baseline, during treatment, and post treatment); (2) data that do not conform to a normal distribution will be expressed as median (IQR), with between-group comparisons executed using the Mann-Whitney *U* test; (3) categorical data will be described in terms of proportions or percentages, with between-group comparisons conducted using chi-square tests or Fisher exact test, depending on the final sample size. (4) All data processing and chart generation will be performed using R 4.0 software (R Project for Statistical Computing). Statistical tests will be 2-sided, with a significance level at *P*<.05.

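### HECSI and NRS are both listed as primary, yet the Per Protocol Set treats HECSI as the primary end point and every test is at 0.05, so the deciding result and its error rate are not fixed

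*Protocol article*

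**What the plan says.** **Number of primary outcomes.** The abstract (Methods) says: "The primary outcome metrics are the Hand Eczema Severity Index (HECSI) and the Numerical Rating Scales (NRS"). The body repeats this, with HECSI and NRS as the two entries under Primary Outcomes. In Data Analyses, members of the Per Protocol Set must "possess complete data for the primary end point (HECSI score"). The singular is used and NRS is not mentioned.

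**Level of testing.** Data Analyses closes with one rule for everything: "Statistical tests will be 2-sided, with a significance level at *P*<.05". It gives no order of testing, no division of alpha and no either/both rule. Sample Size calls the trial noninferiority and uses alpha 0.025, power 0.9 and margin 0.095. Its endpoint is a responder rate by the Nimodipine method (53% against 73.47%), which is not listed as a primary outcome.

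**Timing.** The abstract says "Both groups will be treated with either the active drug or a placebo for 4 weeks" and then "The outcomes will be assessed at the start of the study and again at 2 and 4 weeks after the treatment period". Outcome Measures says all outcome measurements "will be documented from baseline to the conclusion of treatment".

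**NRS recall.** The Numerical Rating Scale section says: "Patients report a numerical value reflecting the average intensity of itching experienced over the preceding 24 hours or the past week".

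**The concern.** A confirmatory trial needs one stated result, or one stated combination of results, that decides it. Here the text supports three readings: HECSI alone decides, either scale decides, or both must succeed. They have different operating characteristics, and nothing in the article chooses among them. If the choice is left until the data are known, the headline can be whichever scale came out well, and the stated 5% no longer describes the chance of a false claim.

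The inconsistency also affects who is analysed. A participant with HECSI but no NRS stays in the Per Protocol Set, while one with NRS but no HECSI leaves it. That fits HECSI as sole primary but not two primaries of equal standing.

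The timing and recall wording adds to this. As written, a primary reading could fall during treatment or after it, and itch could be averaged over a day or over a week.

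**Working it through.** **1. Inputs.** From Sample Size: P_C = 0.53, P_T = 0.7347, δ = 0.095, z = 1.95996 and 1.28155, attrition 15%. From Data Analyses: two-sided 0.05 for all tests. The article gives no correlation between HECSI and NRS, so a range of 0 to 0.9 is assumed.

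**2. The plan's own figure.** Its equation 1 gives

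n = (1.95996 + 1.28155)² × [0.53 × 0.47 + 0.7347 × 0.2653] / (0.53 − 0.7347 − 0.095)² = 51.94, so 52 per group.

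The article states 53, so the figure is reproduced to within one participant. The attrition step, 53 × 1.15 = 60.95, gives 61 per group and 122 in total, as stated. The calculation is for one responder rate and makes no allowance for a second primary outcome.

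**3. HECSI alone.** The error is 5% two-sided, or 2.5% one-sided. Nothing changes.

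**4. Either scale suffices.** For independent tests:

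- two-sided: 1 − 0.95² = 9.75%
- one-sided: 1 − 0.975² = 4.94%

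For correlated tests, the two-sided error is 1 − P(|Z₁| < 1.96 and |Z₂| < 1.96) and the one-sided error is 1 − P(Z₁ < 1.96 and Z₂ < 1.96), from the bivariate normal distribution.

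**5. Both must succeed.** Error is not inflated. If each scale had 90% power, joint power is 0.9 × 0.9 = 81% when independent, and higher with positive correlation.

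| Assumed correlation | Either, two-sided 0.05 | Either, one-sided 0.025 | Both, joint power at 90% each |
|---|---|---|---|
| 0 | 9.75% | 4.94% | 81.0% |
| 0.3 | 9.51% | 4.76% | 82.2% |
| 0.5 | 9.07% | 4.54% | 83.2% |
| 0.7 | 8.35% | 4.17% | 84.7% |
| 0.9 | 7.04% | 3.52% | 86.9% |

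**6. What two primaries would cost, for scale only.** This borrows the plan's responder rates, which were not given for HECSI or NRS.

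- Splitting alpha (one-sided 0.0125 each): 62 per group before attrition. At 53 per group, power falls from 90.6% to 84.9%.
- Requiring both, independent, with 90% joint power: each needs √0.9 = 94.87% power, so 64 per group before attrition.

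**7. Timing, side by side.** With 4 weeks of treatment, the abstract's wording read literally means weeks 6 and 8. Outcome Measures ends at week 4. Intervention has biweekly dispensing and a week 4 visit for drug return, and Safety Assessment has tests after 4 weeks of treatment. Both agree with Outcome Measures. Data Analyses, on the other hand, speaks of time points that include a post-treatment one: "repeated measures ANOVA will be applied for comparisons across multiple time points (eg, baseline, during treatment, and post treatment"). The timeline figure is not available here and may settle the matter.

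**The case against.** **Multiplicity rules often sit in a SAP, and this is an article.** True, and the lack of a rule alone would not be a finding. But the article itself contradicts the number of primary outcomes and itself states a blanket 0.05 level. A SAP could resolve this only by overriding one of those passages. It is also fair that the Per Protocol wording is a completeness criterion and does not say sole; that HECSI alone is meant is an inference from the singular.

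**The 9.75% uses the wrong frame.** It counts significant differences in either direction. For a noninferiority trial at one-sided 0.025, the relevant figure is about 3.5% to 4.9% against 2.5%. This stands, so both scales are given. Data Analyses does state two-sided 0.05, so neither frame can be dismissed from the text.

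**A reader might infer an error of about 16% or more from two scales at two visits** (1 − 0.95⁴ = 18.5% if all four tests were independent). The article does not support this. It assigns repeated measures ANOVA to comparisons across time points and nowhere says that each visit is a separate chance of success.

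**A reader might infer that the planned 90% power is lost.** The article does not show that either. The 90% is for a Nimodipine-method rate, and no power is given for a HECSI or NRS score. The 81% to 87% is conditional on an assumption.

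**A reader might infer that the deciding assessment is 4 weeks after treatment stops.** That rests on one abstract sentence, which most of the body contradicts, and it is probably loose wording. The NRS recall phrase may likewise be a generic description of the instrument. Both are wording corrections.

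**Conclusion.** The concern holds. The article gives two primary outcomes in the abstract and under Primary Outcomes, treats HECSI as the primary end point in Data Analyses, and tests everything at two-sided 0.05 without saying how the two scales combine. The error rate is therefore not fixed. It is 5% if HECSI alone decides and about 7.0% to 9.75% if either scale suffices; on the design's one-sided scale, the corresponding figures are 2.5% and about 3.5% to 4.9%. If both must succeed there is no inflation, and the price is power: about 81% to 87% jointly, if each scale had 90%. These ranges rest on assumed correlations of 0 to 0.9.

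The documents do not show that error is inflated, since that follows only under the either-scale reading. What they show is that the reading has not been chosen.

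**What to change.** 1. Reconcile the abstract, Primary Outcomes and Data Analyses by naming HECSI at the end of the 4-week treatment as the single primary endpoint, which the Per Protocol definition already implies.
2. State HECSI in a form to which the noninferiority margin applies. The 0.095 is a difference in proportions and cannot be used on a HECSI score; a responder rate based on HECSI improvement is one option. Confirm that the 53% and 73.47% used for sizing fit that definition.
3. Test NRS at the same visit only if HECSI noninferiority is shown, with its own hypothesis stated. This fixed order protects the error rate without adding participants.
4. If the sponsor prefers to keep both as co-primary, state that both must succeed and restate the power for the two scales together.
5. Correct the abstract's assessment times to agree with Outcome Measures, if that is the intended schedule.
6. Use one NRS recall period for every participant and visit.

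The cost is wording in the protocol and SAP, one line on the NRS form, and the loss of primary status for NRS. Option 4 avoids that loss but may need more participants. On the article's own timetable (40 recruited by July 1, 2025, recruitment to March 2026, unblinding only after case collection is complete), the change can be made before unblinding.

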**Results:**

The study will be conducted according to the guidelines and regulations approved by the participating institutions. Recruitment is expected to commence in March 2025 and conclude in March 2026. Data collection is anticipated to be completed by June 2026, with the study expected to conclude in August 2026.

**Conclusions:**

This protocol addresses the limitations of previous research and aims to explore the efficacy and safety of RZZYL in treating CHE through a higher-quality clinical study. It seeks to provide additional treatment options for patients with CHE who are resistant to or have poor responses to current therapies.

## Introduction

Eczema is a type of inflammatory disorder that affects the dermis and epidermis. It is caused by both internal and environmental factors. This prevalent clinical condition is categorized into acute, subacute, and chronic eczema according to its progression and clinical features. The hands are a common site for the onset of this condition. Chronic hand eczema is characterized by episodes that occur at least twice a year or persist for more than 3 months during each occurrence. Clinically, chronic hand eczema (CHE) is distinguished by dermal thickening, lichenification, hyperkeratosis, and pruritus [1]. CHE is highly prevalent in the general population, with studies worldwide reporting an incidence rate of 4.0% in the general population and up to 14.5% of individuals experiencing the condition throughout their lifetime [2]. This disorder has become a significant global public health issue in recent years.

At present, there are no medications sanctioned by the US Food and Drug Administration (FDA), specifically for CHE, and a significant unmet demand persists for effective treatments to attain long-term management of CHE [1]. Topical treatment is the conventional method for CHE, and topical corticosteroids (TCS) are the primary suggested therapy. Nevertheless, up to 65% of cases encounter recurrence, skin shrinkage, and other adverse outcomes post treatment, and no evidence indicates that TCS can achieve long-term management of CHE [3]. Calcineurin inhibitors, as an alternative to TCS, can be used for long-term maintenance therapy. These agents help regulate the immune system and reduce inflammation. However, their clinical efficacy in treating skin thickening and lesion-like changes remains suboptimal [4,5]. While some studies have demonstrated that crisaborole (a phosphodiesterase four inhibitor), delgocitinib [6], and ruxolitinib effectively treat hand eczema, large-scale clinical trials are still needed to confirm their efficacy and safety. Furthermore, the high costs associated with these medications impose a significant financial burden on patients [7]. Consequently, current treatment options for CHE in Western medicine remain limited, highlighting an urgent clinical need to identify alternative medications that specifically target the keratotic hyperplasia symptoms associated with CHE.

Traditional Chinese medicine (TCM), as a form of complementary and alternative medicine, has a longstanding history of usage in China for the treatment of hand eczema and remains widely practiced both domestically and internationally [8]. As a unique part of TCM diagnostic and therapeutic techniques, the external treatments of TCM have a long history of success in treating dermatological disorders. Over-the-counter TCM topical preparations, such as Qingpeng Ointment and Longzhu Ointment, are commonly used in China for the treatment of hand eczema. These preparations are adequate for anti-inflammatory and anti-itch therapies. However, Qingpeng Ointment is suitable for acute and subacute eczema, demonstrating limited efficacy for chronic eczema [9,10]. In contrast, Longzhu Ointment is primarily used for treating acne, with no clinical trial evidence supporting its use in treating eczema [11].

Runzaozhiyang lotion (RZZYL) is derived from the *Galla chinensis* ointment developed by [name], the founder of the Department of Dermatology at the China Academy of Chinese Medical Sciences, Guang’anmen Hospital. It combines the traditional *Galla chinensis* ointment formula with the clinical experience of the esteemed Beijing physician, [name]. This formula has established itself as one of the standard prescriptions in the Department of Dermatology at Guang’anmen Hospital, demonstrating apparent clinical efficacy. The primary ingredients of RZZYL comprise *Galla chinensis*, *Tribulus terrestris, Cannabis fructus, Bletilla striata, Cnidium monnieri* (L) Spreng, and *Sophora flavescens* Aiton. Pharmacological research has underscored the diverse therapeutic properties associated with these components (given in Table 1). Our preliminary investigation suggests that this formula exhibits a markedly superior efficacy rate relative to placebo in the treatment of CHE. However, there is a lack of high-quality randomized controlled trials, and the current evidence is insufficient to validate the effectiveness and safety of RZZYL for CHE. Therefore, our study aims to thoroughly evaluate the efficacy and safety of RZZYL for treating CHE through a carefully designed randomized controlled trial.

**Table 1. T1:** Overview of Runzaozhiyang lotion.

Chinese name	Common name	Latin name	Species and family	Proportion (%)	Efficacy
Wubeizi	Chinese Nutgall	*Galla chinensis*	The female aphids of *Aphis gossypii* or *Aphis craccivora* from the Aphididae family of the Hemiptera order, after piercing the tender leaves or petioles of *Rhus chinensis* (or its related species), parasitize them to form galls. These galls can be obtained by baking and drying them.	22.2	Antibacterial and anti-inflammatory effects [12]
Baijili	Caltrop	*Tribulus terrestris*	The mature dried fruits of *Tribulus terrestris*.	22.2	Antibacterial and anti-inflammatory effects [13]
Huomaren	Hemp Fruit	Cannabis fructus	The dried mature fruits of the Moraceae family plant *Cannabis sativa* L.	22.2	Antibacterial, anti-inflammatory, lipoid-regulating, and immunomodulatory properties effects [14]
Baiji	*Bletilla striata*	*Bletilla striata*	The tubers (or bulbs) and underground corms, after being washed, soaked, or blanched, are sliced thinly and then dried in the sun.	11.1	Wound healing, antibacterial, and anti-inflammatory effects [15,16]
Shechuangzi	Common Cnidium Fruit	*Cnidium monnieri* (L) Spreng	The dried mature fruits of the Apiaceae plant *Cnidium monnieri* (L) Cuss.	11.1	Antipruritic, antibacterial, and anti-inflammatory effects [17,18]
Kushen	Light yellow Sophora Root	*Sophora flavescens* Aiton	The dried roots of the leguminous plant *Sophora flavescens* Ait.	11.1	Antipruritic, antioxidant, and anti-inflammatory effects [19,20]

## Methods

### Trial Design

The trial is randomized, double-blind, double-dummy, and positive drug-controlled. The research will be carried out at Guang’anmen Hospital of the China Academy of Chinese Medical Sciences. Before therapy, patients with CHE have standardized baseline examinations, including medical history, physical examination, specialist assessments, and laboratory tests. Dermatologists will conduct the evaluation scales. The hospital’s laboratory and electrocardiogram departments will test blood, urine, and electrocardiogram. All enrolled patients will be randomly assigned to 2 groups: RZZYL (granules) plus mometasone furoate cream placebo and RZZYL (granules) placebo plus mometasone furoate cream. The treatment method for each patient will be the same within their respective groups. The trial will comply with the World Medical Association Declaration of Helsinki and China’s legislation and recommendations on Good Clinical Practice. Informed consent will be acquired from all participants after a comprehensive explanation by the doctors prior to the intervention. The study design is illustrated in Figure 1.

**Figure 1. F1:**
[figure not shown]
Flow diagram of the randomized double-blind study on the treatment of chronic hand eczema with the Runzaozhiyang Lotion. ALP: alkaline phosphatase; ALT: alanine aminotransferase; AST: aspartate aminotransferase; CHE: chronic hand eczema; Cr: creatinine; DBIL: direct bilirubin; DLQI: dermatology life quality index; γ-GGT: gamma-glutamyl transferase; HECSI: Hand Eczema Severity Index; IGA: Investigator Global Assessment; MFC: mometasone furoate cream; NRS: numerical rating scale; POEM: Patient-Oriented Eczema Measure; RZZYL: Runzaozhiyang lotion; TBIL: total bilirubin.

### Sample Size

This trial aims to objectively assess the efficacy and safety of RZZYL for CHE through a high-quality clinical study design, thereby providing substantial data support for medication development and translation. The trial uses mometasone furoate cream as the positive drug control, categorizing it as a noninferiority trial. According to pertinent literature, the efficacy rate of mometasone furoate cream for treating HE, as assessed by the symptom improvement index using the Nimodipine method, is 53% [21]. Based on previous clinical observations, the efficacy rate for the RZZYL (granules) group is 73.47% [22]. Using the noninferiority study formula (equation 1) [23], with a statistical power (1-β) set at .9, an alpha level (α) of .025, and a noninferiority margin (δ) of 0.095 [24], the values for z_α_ and z_β_ are 1.95996 and 1.28155, respectively, with k (prespecified noninferiority margin) set to 1. The symbol “z” typically represents the critical value in a standard normal distribution, used to calculate the critical region in hypothesis testing. The sample size calculation indicates that the control group requires approximately 53 participants (n_c_). Consequently, the sample size for the experimental group (n_t_) is calculated as k×n_c_=53 participants, leading to a total sample size of 106 participants. Considering an anticipated attrition rate of 15.0% [25], the necessary sample size is adjusted to 61 participants for both the control and experimental groups, resulting in a total required sample size of 122 participants.

(1)
$$n_{c}=\frac{\left(Z_{1-\alpha }+Z_{1-\beta }{)}^{2}\cdot [P_{C}(1-P_{C})+P_{T}(1-P_{T})\right]}{(P_{C}-P_{T}-\delta {)}^{2}}$$

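### The 90% noninferiority power depends on a true 20.5-point RZZYL advantage (16-22% at equal efficacy), and the two-sided difference tests named do not use the 0.095 margin

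*Protocol article*

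**What the plan says.** The Sample Size section fixes the type of trial: "The trial uses mometasone furoate cream as the positive drug control, categorizing it as a noninferiority trial". It takes the control rate from the literature, "as assessed by the symptom improvement index using the Nimodipine method, is 53" percent, and the RZZYL rate from a separate source: "Based on previous clinical observations, the efficacy rate for the RZZYL (granules) group is 73.47" percent. The other inputs are "statistical power (1-β) set at .9", "an alpha level (α) of .025" and a margin of 0.095. Equation 1 then gives 53 per arm, raised to 61 per arm (122 in total) for 15% attrition. The same paragraph describes the allocation ratio as follows: "with k (prespecified noninferiority margin) set to 1".

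The primary outcomes are HECSI and NRS. The secondary outcomes are target lesion area, POEM, DLQI and IGA. No responder or efficacy rate is listed.

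Data Analyses assigns continuous data to t tests, repeated measures ANOVA or the Mann-Whitney test. Categorical data are described as proportions, "with between-group comparisons conducted using chi-square tests or Fisher exact test". The general rule is: "Statistical tests will be 2-sided, with a significance level at" P<.05. The section mentions neither the margin nor noninferiority.

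**The concern.** A reader who is told noninferiority with power .9 will normally take it that a product about as good as the active control has a high chance of success. Here it does not. Most of the distance that drives the sample size is an expected advantage of RZZYL over the steroid, taken from two separate sources. The article cites no head-to-head comparison for it, and its Introduction calls the current evidence on RZZYL insufficient.

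The named tests raise a second problem. A two-sided test of difference has zero difference as its null hypothesis. A non-significant result does not show that RZZYL is within 9.5 points of mometasone. Only a significant result in RZZYL's favour would settle noninferiority, and it would do so by showing superiority, a harder target than the one the trial was sized for.

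**Working it through.** **Inputs** (Sample Size): P_C = 0.53, P_T = 0.7347, margin 0.095, z values 1.95996 and 1.28155, allocation 1:1.

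**Reproducing the plan's figure.**
- Variance term: 0.53 × 0.47 + 0.7347 × 0.2653 = 0.2491 + 0.1949 = 0.4440.
- Distance: 0.53 - 0.7347 - 0.095 = -0.2997, squared 0.08982.
- n = (1.95996 + 1.28155)² × 0.4440 / 0.08982 = 10.507 × 0.4440 / 0.08982 = 51.94.

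This rounds up to 52, against about 53 stated, so the figure reproduces closely enough. Of the 0.2997, 0.2047 (68%) is assumed superiority and 0.095 is the margin.

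**Evaluable numbers.** 61 × 0.85 = 51.85, so about 52 per arm remain after the planned attrition. The upper limit is 61 per arm with no loss.

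**Noninferiority power** = Φ((P_T - P_C + 0.095)/SE - 1.95996), with SE = √([P_C(1 - P_C) + P_T(1 - P_T)]/n).
- Planning rates, n = 52: SE = √(0.4440/52) = 0.0924; 0.2997/0.0924 - 1.960 = 1.283; power 90.0%.
- 53% in both arms, n = 52: SE = √(0.4982/52) = 0.0979; 0.095/0.0979 - 1.960 = -0.989; power 16.1%.

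| True rates, RZZYL vs mometasone | 52 per arm | 61 per arm |
|---|---|---|
| 73.47% vs 53% | 90.0% | 94.0% |
| 63% vs 53% | 52.6% | 59.2% |
| 53% vs 53% | 16.1% | 18.2% |
| 73.47% vs 73.47% | 19.4% | 22.0% |

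Exact binomial enumeration of the same decision rule at 53% in both arms gives 17.6% (52 per arm) and 20.7% (61 per arm), inside the 16-22% range.

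**Two-sided difference test on the responder rate.** This applies only if the rate used for sizing were tested as Data Analyses describes for categorical data. By exact enumeration at 73.47% vs 53%, chi-square has power 60.0% with 52 per arm and 65.6% with 61. Fisher has 51.7% and 58.5%. The smallest expected cell at 52 per arm is 52 × (0.47 + 0.2653)/2 = 19.1, so Fisher is unlikely to be needed.

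**HECSI and NRS.** No mean difference, standard deviation or margin on either scale is given. The 0.095 is a difference in proportions and does not carry over. Power for these outcomes cannot be computed from the article.

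**The case against.** The strongest reply is that nothing is miscalculated. Every power figure is conditional on its inputs, the section prints both rates, the margin and the formula together, and assuming an advantage when sizing a noninferiority trial is permissible. That stands. The sample size is not an arithmetic error, and the inputs are not concealed. What the section omits is the consequence: it gives .9 as the power of a noninferiority trial without saying that this requires a 20.5-point advantage.

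A reader might also infer that the trial's power under its stated analysis is only 52-66%. The article does not support that. Chi-square and Fisher are its general choice for categorical data, whereas the named primary outcomes are scores that would go to other tests. The 60-66% holds only if the responder rate is tested for difference, and the lower Fisher figures concern a test unlikely to be used.

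Nor can an interval be put around 73.47% to show how uncertain it is, because the article does not give the number of patients behind it.

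A confidence-interval method may be set out in a statistical analysis plan that is not shown. This limits the point to what the article itself states: noninferiority sizing on a responder rate, followed by two-sided tests of difference and a list of outcomes without that rate. These statements do not fit together.

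The label on k is a slip of wording. The same paragraph multiplies n_c by k to get 53, and allocation is 1:1 elsewhere, so no number changes.

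**Conclusion.** The point holds in this form. The stated power is correct at 73.47% versus 53%: 90-94% with 52 to 61 evaluable per arm. It falls to 53-59% for a true 10-point advantage over a 53% control rate, and to 16-22% at equal efficacy (common rate 53% or 73.47%). These figures use the plan's margin of 0.095, one-sided 0.025 and the unpooled normal approximation of equation 1.

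The two-sided tests of difference in Data Analyses do not match this sizing and cannot establish noninferiority short of superiority. The endpoint behind the sample size is missing from the listed outcomes, so the 90% attaches to no named primary analysis. Power for HECSI and NRS is unknown from the article; it has not been shown to be low.

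**What to change.** 1. State in Sample Size that the 90% is conditional on true rates of 73.47% and 53%, an advantage of 20.5 points, and that power is about 16-22% if the two treatments are equally effective.
2. Reconcile the responder rate with the primary outcomes: list it as the endpoint of the noninferiority test, with the response definition used for sizing, and state how it relates to HECSI and NRS.
3. For that endpoint, replace the two-sided test of difference with the two-sided 95% confidence interval for RZZYL minus mometasone. Noninferiority is shown if the lower limit lies above -9.5 points. If it is shown, superiority may be read from the same interval (lower limit above 0) in fixed sequence at no cost in alpha.
4. Relabel k as the allocation ratio.

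The cost is wording in the protocol and the analysis plan. No extra patients are proposed. The drawback is a less favourable statement of power. The article reports 40 patients recruited by July 1, 2025 and unblinding only after case collection is complete, so the change can be made before any unblinded result is known.
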